## Abstract

**Background:**

People with decompensated cirrhosis require complex medical care and are often prescribed an intricate and frequently changing medication and lifestyle regimen. However, many patients mismanage their medications or have poor comprehension of their disease and self-management tasks. This can lead to harm, hospitalization, and death.

**Methods/design:**

A patient-oriented education and medication management intervention has been developed for implementation at a tertiary hospital hepatology outpatient center in Queensland, Australia. Consenting patients with decompensated cirrhosis will be randomly allocated to education intervention or usual care treatment arms when they attend routine follow-up appointments. In the usual care arm, participants will be reviewed by their hepatologist according to the current model of care in the hepatology clinic. In the intervention arm, participants will be reviewed by a clinical pharmacist to receive the education and medication management intervention at baseline in addition to review by their hepatologist. Intervention participants will also receive three further educational contacts from the clinical pharmacist within the following 6-month period, in addition to routine hepatologist review that is scheduled within this time frame. All participants will be surveyed at baseline and follow-up (approximately 6 months post-enrollment). Validated questionnaire tools will be used to determine participant adherence, medication beliefs, illness perceptions, and quality of life. Patients’ knowledge of dietary and lifestyle modifications, their current medications, and other clinical data will be obtained from the survey, patient interview, and medical records. Patient outcome data will be collected at 52 weeks.

**Discussion:**

The intervention described within this protocol is ready to adapt and implement in hepatology ambulatory care centers globally. Investigation of potentially modifiable variables that may impact medication management, in addition to the effect of a clinical pharmacist-driven education and medication management intervention on modifying these variables, will provide valuable information for future management of these patients.

**Trial registration:**

Australian and New Zealand Clinical Trial Registry identifier: ACTRN12616000780459. Registered on 15 June 2016.

**Electronic supplementary material:**

The online version of this article (doi:10.1186/s13063-017-2075-4) contains supplementary material, which is available to authorized users.

## Background

The morbidity and health care costs associated with decompensated cirrhosis are substantial because patients require complex medical care to manage debilitating complications of their disease [1, 2]. People with decompensated cirrhosis are often prescribed multiple medications for therapeutic or prophylactic use to reduce the negative health effects of cirrhosis. However, many patients lack the knowledge and skills required to contribute effectively to disease management [3, 4].

On average, this patient group has approximately three hospital admissions each year [1, 5], reflecting the high burden of illness and use of health care resources. The number of medications prescribed on hospital discharge has been found to predict rehospitalization rate and time to first hospital readmission, independently of serum biomarkers that also predict poor outcomes [2]. With recurrent admissions, more medicines are prescribed and/or the medication regimen is altered. This increases opportunities for miscommunication and nonadherence, thereby increasing the risk of medication errors and rehospitalization.

Poor knowledge of cirrhosis, medications, self-monitoring, and important dietary and lifestyle modifications has been described in ambulatory Australian patients with cirrhosis [4]. Low medication adherence was identified in over one-fourth of patients (27.5%), and discrepancies among conventional medications were also seen in 54.0% of patients with cirrhosis attending general hepatology clinics [6]. Communication barriers between patients and clinicians are a recognized impediment to patient care that may result in clinically significant discrepancies and other medication-related problems (MRPs) [7]. MRPs are events or circumstances involving medications that actually or potentially interfere with an optimum outcome of care [8]. They are complex and multifaceted issues that may be the result of numerous interacting factors. Examples of MRPs that may occur in patients with decompensated cirrhosis are presented in Table 1. It has been estimated that up to 22% of 30-day readmissions among patients with decompensated cirrhosis may be preventable with improved medication management or more frequent monitoring [2].

**Table 1 Tab1:** Potential medication-related problems in patients with decompensated cirrhosis

Classification and definition	Subtype	Example
Adverse drug reaction		
A medical problem resulting from an adverse effect of a drug. These include sensitivities, intolerances, and immune-mediated hypersensitivity reactions.	Minor	Minor dizziness related to propranolol; manage with lifestyle counseling.
	Moderate	Gynecomastia related to spironolactone; may require dose adjustment or cessation.
	Severe	Stevens-Johnson syndrome precipitated by sulfamethoxazole-trimethoprim (Bactrim DS®).
Drug interactions		
An actual or potential medical problem that is related to a drug-drug or drug-patient interaction.	Drug-drug	Harvoni® (Gilead Sciences, Foster City, CA, USA) and amiodarone.
	Drug-patient	Hepatorenal syndrome precipitated by NSAID use.
Drug use without indication		
The patient is taking a medication for no medically valid reason.		Proton pump inhibitor use in a patient without gastroesophageal reflux disease, peptic ulcer, or variceal bleeding.
Incorrect dosage		
A medical condition that is being treated with drug therapy; however, the dose may be too low or too high.	Subtherapeutic	10-ml daily dose of lactulose, achieving one bowel motion every second day.
	Supratherapeutic	Spironolactone 400 mg daily in a patient with minimal abdominal ascites.
Nonadherence		
The patient is prescribed a drug for a medical condition but is not taking it for psychological, sociological, or economic reasons.	Unintentional	Forgetting to take propranolol at nighttime.
	Intentional	Not taking lactulose because of side effects (flatulence, bloating) or cost following removal from the Pharmaceutical Benefits Scheme.
Untreated indications		
A medical condition that requires drug therapy but is not being treated with medication. This may be related to intentional or unintentional nonadherence by the patient, or to intentional or unintentional underprescribing by a medical practitioner.	Nonadherence	As above.
	Underprescribing	Low cholecalciferol and tocopherol identified by pathology, not supplemented. Unintentional – oversight. Intentional – patient unable to afford currently; to be reconsidered at next visit.

*NSAID* Nonsteroidal anti-inflammatory drug

In existing models of collaborative outpatient practice, integrated pharmacist education and medication management interventions have been shown to improve patient knowledge, adherence, and outcomes in chronic diseases that have complex medication management issues similar to those of cirrhosis [9–13]. Identification of medication discrepancies and MRPs using a clinical pharmacist’s reconciled medication record reduces harm and hospitalization and may allow for simplification of the prescribed regimen [14, 15]. The association between patient knowledge, polypharmacy, poor adherence, and medication discrepancies has not been investigated in patients with decompensated cirrhosis to date. It is hypothesized that addressing this complicated relationship by implementing a targeted patient education and medication management intervention in a multidisciplinary model of hepatology ambulatory care may improve medication management, reduce MRPs, and improve medication-related outcomes for people with decompensated disease.

## Methods/design

### Study aims and hypotheses

The primary aim of the study is to determine whether the intervention (medication review, reconciliation, and additional education by a clinical pharmacist) reduces the frequency (counts) and severity (measure of clinical significance) of discrepancies between patient-reported and medical record-documented “current” medications. The secondary aims are to describe the impact of the intervention on medication adherence, quality of life (QoL), medication and illness beliefs, patient knowledge of disease and self-management tasks related to decompensation history and prescribed therapy, and the frequency of hospitalization for management of cirrhosis-related complications, non-cirrhosis-related complications, and survival. The sustainability of the intervention in the current health care system in relation to costs and cost-effectiveness will also be evaluated.

#### Hypotheses

Compared with patients receiving usual care, patients who receive the tailored (additional) education and medication management intervention are hypothesized to benefit in the following ways:

(H1) Fewer medication discrepancies

(H2) Improved medication adherence

(H3) Improved QoL

(H4) Improved illness perceptions

(H5) Improved medication beliefs

(H6) Improved knowledge of disease self-management tasks related to prescribed medications

(H7) Fewer hospital admissions

(H8) Longer survival time

### Design and setting

The study has a randomized, controlled, parallel-group design and will be conducted at a single site, the Hepatology Outpatient Centre at the Princess Alexandra Hospital (PAH), located in Brisbane, Australia. The Gastroenterology and Hepatology Department at the PAH is one of the largest hepatology centers in Australia and the only liver transplant center in Queensland. The hospital’s local catchment area is 3,856 km^2^. Additionally, many patients travel from regional and remote areas, including interstate to access specialist services. Consequently, the Hepatology Outpatient Centre is responsible for the ambulatory care of a significant proportion of southeastern Queensland patients with chronic liver disease (CLD).

### Participants

#### Eligibility criteria

Eligible participants are (1) adults aged ≥18 years; (2) diagnosed with hepatic cirrhosis by a hepatologist; and (3) current or recent (within the preceding 2 years) chronic liver failure-related complication(s), including ascites, variceal bleeding, spontaneous bacterial peritonitis, sepsis, encephalopathy, or liver-related renal dysfunction. Liver biopsy, ultrasound, and FibroScan® technology (Echosens, Paris, France) will be used to confirm the diagnosis of cirrhosis if available [16, 17]. Patient medical records and correspondence letters will be used to identify history of chronic liver failure-related complications.

#### Exclusion criteria

Individuals will be excluded for (1) inability to provide informed consent and/or (2) receiving intensive management by other health care teams (i.e., liver transplant team, palliative care).

### Participant recruitment

The Hepatology Outpatient Centre’s appointment database will be prescreened for eligible participants who are scheduled for routine review by a hepatologist. Persons identified as eligible will be contacted via telephone in the week preceding their appointment to discuss the study and offer participation. Participants will be given instructions to arrive 15 minutes early for their appointment, bring all medications to the clinic, and ask their carer or responsible family member to accompany them if appropriate. Consented participants will be randomly allocated to one of the two study arms: (1) intervention or (2) usual care.

### Randomization and allocation

An independent person at the PAH will prepare individual envelopes labeled with the randomization number and containing the corresponding study arm. Allocation concealment will be achieved by use of sequentially numbered, sealed, opaque envelopes that will be stored and opened in order by a third party located within PAH.

### Study navigation

Figure 1 describes the planned study flow, including data collection time points. A Standard Protocol Items: Recommendations for Interventional Trials (SPIRIT) checklist of standard protocol items [18] addressed within the study protocol is provided in Additional file 1.

**Fig. 1 Fig1:**
[figure not shown]
Standard Protocol Items: Recommendations for Interventional Trials (SPIRIT) flow diagram of participant recruitment and study navigation. *MRP* Medication-related problem

All participants will complete a baseline survey prior to their scheduled outpatient clinic review. Validated questionnaire tools will be used to determine baseline medication adherence, medication beliefs, illness perceptions, and QoL, in addition to patient knowledge of important dietary and lifestyle modifications. The survey will be completed with a study coordinator over the telephone or in person in a private clinic room, or it will be self-completed by the participant in the clinic waiting room. Patient carers or family members will be involved if necessary.

Usual care participants will subsequently receive routine review and education by their hepatologist according to the current model of care in the hepatology clinic. Intervention participants will be reviewed by a clinical pharmacist to receive the education and medication management intervention (described below) in addition to routine review and education by their hepatologist. Intervention participants will also receive three further educational contacts from the clinical pharmacist in addition to scheduled routine hepatologist review within the following 6-month period.

All participants will be resurveyed at follow-up (*t*
_3_, approximately 6 months post-enrollment) to explore changes in their medication adherence, medication beliefs, illness perceptions, QoL, and knowledge. Patient outcome data will be collected at 52 weeks (*see* “Study endpoints and data collection” section below).

### Intervention development

A multifaceted, clinical pharmacist-driven education and medication management intervention targeted to patients with decompensated cirrhosis was developed by a panel of clinicians (including a hepatologist, general physician/pharmacologist, clinical nurse, and clinical pharmacist). Education and monitoring points (Table 2) were agreed upon on the basis of clinical hepatology guidelines to augment and support information provided by hepatologists and other clinicians involved in patient care.

**Table 2 Tab2:** Medication-related education provided to intervention participants receiving pharmacotherapy for chronic liver failure-related complications

Clinical decompensation history	Advice	Monitoring
Ascites		
	Adherence with diuretics Do not add salt to food or when cooking Restaurant meals, take-out foods, and tinned foods generally contain high levels of sodium Sea salt, Himalayan rock salt, and table salt have similar sodium content Caution with salt substitutes—may contain high levels of potassium Avoid nonsteroidal anti-inflammatory analgesics Highly educated and/or engaged participants: restrict sodium intake to 2000 mg daily	Weigh self weekly if dose of diuretics is stable and ascites is well-controlled Weigh self daily if diuretic dose changes or poorly controlled ascites; notify clinic if postural symptoms/dizziness develop Document weight – do not just “remember” Do not restrict fluid intake unless advised to by a doctor Development of fevers and/or chills accompanied by abdominal pain and/or discomfort—present to the emergency department for assessment
Encephalopathy		
	Adherence with lactulose (with or without rifaximin) Do not drink alcohol Avoid sleeping tablets and opiate analgesics Do not drive unless your doctor has told you it is okay to do so Medication assistance may be required in severe memory disturbance Highly educated and/or engaged participants: discuss accumulation of ammonia and other toxins	Be mindful of worsening mood disturbances, personality changes, and sleep inversion Family member or carer to help monitor for signs of deterioration Titrate lactulose dose to achieve two or three loose bowel motions daily; reduce/withhold if diarrhea or severe bloating occurs Violent, irrational behavior or loss of consciousness—call an ambulance immediately
Hepatocellular carcinoma		Attend follow-up ultrasound appointments as scheduled
Jaundice, itch		
	Antihistamines are not very effective Use soap-free body wash Moisturize skin daily	Get blood tests as directed Acute or recurrent yellowing of eyes and skin—see a doctor as soon as possible
Malnourishment		
	Eat small, frequent meals regardless of appetite Eat a bedtime snack Choose protein- and calorie-rich snacks Take supplements as directed Use an antiemetic if required Do not drink alcohol	Weigh self once weekly Keep a food diary See a dietitian for expert advice
Variceal bleeding		
	Adherence with propranolol (with or without proton pump inhibitor) Highly educated and/or engaged participants: discuss portal hypertension and development of varices	Attend endoscopic surveillance as scheduled Monitor blood pressure, postural symptoms, dizziness Check hemoglobin and iron stores as appropriate Hematemesis or melena—call an ambulance immediately

### Intervention description

During the initial encounter with each intervention patient (and carer/family member if present), the clinical pharmacist will obtain a complete, reconciled list of current medications and identify MRPs. The pharmacist will use open and closed questions to ascertain adherence, other medication-taking behaviors, and medication needs on an individualized basis. Participating patients will receive medication- and lifestyle-related education and advice tailored to their needs (decompensation history and medications) and receptiveness (Table 2). The pharmacist will also collaborate with the patient’s general practitioner and hepatologist to optimize therapy, facilitate resolution of MRPs, and monitor issues where required.

Subsequent contact with participants will be made at 4–6 weeks (*t*
_1_) and 12–14 weeks (*t*
_2_) after the baseline interview to discuss changes in prescribed therapy; identify new MRPs and previously identified MRPs that are ongoing; reiterate advice provided at baseline; and provide additional relevant education about medications, lifestyle modifications, and self-management of cirrhosis to build on previous discussions. Promotion of a patient-clinician partnership will be central to each discussion to encourage functional health literacy and self-efficacy with regard to patient confidence to raise questions and discuss issues with health care providers.

### Medication-related problems

During patient interviews, the clinical pharmacist will identify actual and potential MRPs and document these in the patients’ medical notes and on a structured data collection form. The pharmacist will then facilitate the resolution or monitoring of individual MRPs with other relevant clinicians as appropriate and document each outcome in patients’ medical notes and data collection forms.

The clinical significance of MRPs (and medication discrepancies) will be assessed by a clinician panel using a risk matrix (Fig. 2) modified from the Metro North Health Service Risk Management Framework [19]. The matrix assigns a composite risk of prospective severity and likelihood of potential harm, as well as duration of time until potential harm may occur, as a consequence of the MRP. The panel of clinicians will comprise at least one clinical pharmacist, hepatologist, and general physician/pharmacologist who have experience in managing patients with cirrhosis. MRPs will be de-identified, randomized, and independently assessed by at least two members of the panel. Relevant clinical information will accompany the de-identified MRPs, but not details of patient outcomes or MRP resolution, to ensure unbiased prospective assessment of potential harm. Consensus of individual rankings will be used to determine the final measure of potential harm. Where there is disagreement between individual rankings, a roundtable panel discussion will be called to facilitate consensus.

**Fig. 2 Fig2:**
[figure not shown]
Risk matrix for assessment of significance of medication discrepancies and other medication-related problems

### Tailored intensity intervention

Intervention participants will receive education and advice tailored to their needs, receptiveness, and cognitive barriers. For example, a patient who has nonalcoholic steatohepatitis with well-controlled abdominal ascites and no other decompensation history would likely require a low-intensity intervention if he or she identified as adherent. Low-intensity intervention for this patient would consist of reiteration of important dietary modifications, monitoring of weight, and diuretic education. Conversely, a malnourished ex-alcoholic patient with a history of poorly controlled ascites, recurrent encephalopathy, and persistent hypotension will require high-intensity intervention. This would ideally involve inclusion of a carer/family member in the discussion to educate both parties on the potential precipitants and early signs of encephalopathy, self-titration of lactulose, and when to present to the emergency department. Pharmacotherapy education (including possible discussion of adherence aids), high-protein and low-sodium dietary modifications, daily weight monitoring (including when to contact the clinic if weight is changing significantly over short periods of time), and review of pharmacotherapy that may contribute to hypotension would also be conducted. Liaison with additional health providers may also be required.

After providing education and advice to intervention participants, the clinical pharmacist will use a structured data collection form to record topics that have been discussed, topics that were not discussed and reasons why, and whether a carer was present. Post hoc testing will be employed to explore study outcomes according to the intensity of the intervention received and the completeness of relevant information provided (*see* the “Data analysis” section below).

### Medication reconciliation

Using information from several sources (including the patient, general practitioner, pharmacy, own medications, carer), the clinical pharmacist will construct a reconciled list of current pharmacotherapy. The reconciled list of medications will be made available to other clinicians in the patient’s medical record, and a patient-friendly guide will be constructed using the approved statewide template. This guide will be printed and provided to the patient. The patient will be encouraged to take it to all health care appointments and use it at home to aid with compliance and memory. The guide will also contain additional medication management and lifestyle points related to prescribed therapy, such as low-salt diet reminders for patients who are prescribed diuretics in the management of ascites. Patients will be encouraged to manually edit the medication guide when therapy is altered.

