### Primary outcome

#### Medication discrepancies

Discrepancies between patient-reported and clinician-documented current medications will be obtained via the patient questionnaire (medication recall), patient interview (reconciliation for intervention participants only), and medical record review (clinician documentation). The clinical significance of discrepancies will be determined by blinded comparison at the completion of the study using a risk matrix tool (Fig. 2), which assigns a composite ranking of severity, likelihood, and duration, as described in the Methods subsection “Medication-related problems” above. Discrepancies (between medications, doses, and frequency of administration) will be examined at baseline and follow-up (*t*
_3_) for both groups. A composite endpoint of frequency (counts of) and potential risk will be examined by measuring total frequency of high/very high risk discrepancy occurrence and the frequency of high/very high risk discrepancy occurrence per patient.

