Differences in the study endpoints of interest will be examined between the intervention and control groups at baseline and at follow-up. The endpoints will be examined at baseline to test for homogeneity between groups (effectiveness of randomization) and to identify clinical variables that may influence endpoints (e.g., Model for End-Stage Liver Disease score; Child-Turcotte-Pugh classification; decompensation history, including event date, type, severity, and recurrence; hospitalization frequency; age; sex; biochemical abnormalities; and other prognostic variables). Clinically significant differences at baseline between groups will be adjusted for during the final analysis. Changes in the frequency of medication discrepancies, self-reported adherence, QoL, medication beliefs, illness perceptions, and patient knowledge at follow-up will be examined to measure the effect of the intervention on study outcomes at group and individual levels. The primary endpoint of medication discrepancies will be explored using total frequency of instances and frequency of instances per patient and per medication group. Comparison between intervention and control groups at baseline and *t*
_3_ will be made using total number of instances per group, total number of high/very high risk instances per group, mean/median number of instances per patient, and mean/median number of high/very high risk instances per patient.

Predictors of clinical outcomes will be identified using binary logistic regression to determine the OR (95% CI). A multivariable logistic regression model will be used to determine independent predictors for patient outcomes. The multivariable logistic regression model will be constructed using variables of clinical significance (severity of disease; decompensation history, including date, type, severity, and frequency of events; other prognostic variables) and statistical significance as determined by univariate analysis.

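### The baseline discrepancy count is not tied to pre-intervention sources and is not measured alike in both arms, yet it serves as a clean baseline for change and adjustment

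*Protocol article*

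**What the plan says.** The Primary outcome section (Medication discrepancies) gives three sources for the count. The first is recall: "Discrepancies between patient-reported and clinician-documented current medications will be obtained via the patient questionnaire (medication recall". The other two follow in the same sentence: "patient interview (reconciliation for intervention participants only), and medical record review (clinician documentation". Reconciliation is therefore a source in one arm only. The count is taken twice in both groups: "Discrepancies (between medications, doses, and frequency of administration) will be examined at baseline and follow-up". Table 3 lists interview, questionnaire and record review for discrepancies at t0 and t3.

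The Intervention description places reconciliation at the first visit: "During the initial encounter with each intervention patient (and carer/family member if present), the clinical pharmacist will obtain a complete, reconciled list". The Medication reconciliation section then says where the list goes: "The reconciled list of medications will be made available to other clinicians", in the patient's own medical record.

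The patient-reported side at t0 is better protected. Under Study navigation: "All participants will complete a baseline survey prior to their scheduled outpatient clinic review".

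The Data analysis section uses the t0 endpoints in three ways: to check homogeneity between groups as a test of the randomization, to decide on adjustment ("Clinically significant differences at baseline between groups will be adjusted for during the final analysis"), and to examine changes in discrepancy frequency. It also compares the groups directly at t3.

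**The concern.** A baseline used for change scores or as a covariate must be free of the treatment and measured the same way in each arm. Here two routes make the t0 count depend on the arm.

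- **The record.** From the first encounter, the intervention arm's record can hold the pharmacist's reconciled list. Whether the t0 record review reads documentation from before or after that entry is not stated. The article text also does not fix which of the pharmacist and the hepatologist sees the patient first.
- **The sources.** The reconciliation interview contributes to the count only in the intervention arm. The text states this asymmetry outright.

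The sign of the resulting bias is not known. If the entry resolves discrepancies, the intervention arm's t0 count is too low, and change or baseline adjustment takes away part of the effect. If the fuller list or the interview reveals discrepancies that would stay hidden under usual care, the t0 count is too high and the same analyses overstate the benefit. Either way, a difference produced by measurement or early treatment could be read as imperfect randomization and prompt an adjustment that introduces bias.

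**Working it through.** **Inputs from the document** (Power calculation and Data analysis sections): 3.12 discrepancies per patient reduced to 1.56, so a difference of 1.56; SD 2.5; 41 per arm; two-sided alpha 0.05.

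**Assumptions, not in the document:** the correlation r between the t0 and t3 counts, and the share f of the 1.56 effect already present in the intervention arm's t0 count. A negative f means the t0 count is inflated in that arm. SD 2.5 is taken at both times.

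**Step 1: the plan's own figure.** n per arm = 2 × (1.96 + 0.84)² × 2.5² / 1.56² ≈ 40.3, rounded up to 41. Power at 41 is 80.7% by the normal approximation (79.7% by noncentral t). The stated 41 reproduces, as a simple two-group comparison that makes no use of baseline.

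**Step 2: formulas.**
- t3 comparison alone: effect 1.56, SD 2.5, whatever f is.
- Change from t0: effect 1.56 × (1 − f), SD 2.5 × √(2(1 − r)).
- Adjusted for the t0 count: effect 1.56 × (1 − r·f), SD 2.5 × √(1 − r²). This ignores a small loss of precision from the baseline difference.

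**Step 3: results at r = 0.5, 41 per arm.** The SD is 2.5 for change and 2.5 × √0.75 = 2.17 for the adjusted analysis. Power is by the normal approximation.

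| f | Change (power) | Adjusted (power) | t3 alone (power) |
|---|---|---|---|
| −0.25 | 1.95 (94%) | 1.755 (96%) | 1.56 (81%) |
| 0 | 1.56 (81%) | 1.56 (90%) | 1.56 (81%) |
| 0.25 | 1.17 (56%) | 1.365 (81%) | 1.56 (81%) |
| 0.50 | 0.78 (29%) | 1.17 (69%) | 1.56 (81%) |

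For example, at f = 0.50 change is 1.56 × 0.5 = 0.78 and adjusted is 1.56 × (1 − 0.25) = 1.17.

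**Step 4: sensitivity to r.** At f = 0.50 with r from 0.3 to 0.7, the change estimate stays at 0.78 with power 22% to 45%. The adjusted estimate runs from 1.33 to 1.01, with power 69% to 73%.

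The high power in the first row is no advantage, because it comes from an overstated effect.

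**The case against.** The strongest reply is that contamination through the record is inferred. The article does not say that the t0 review reads documentation made after the pharmacist's entry, or that the reconciled list is the comparator. An extraction cut-off is the kind of detail a full protocol may hold, and the flow figure, which is said to show data collection time points, is not available in the text reviewed. This stands as far as the record route goes: it is possible, not shown. It does not answer the source asymmetry, which the Primary outcome section states, nor the use of the resulting t0 count as a baseline.

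Second, recall is collected before the clinic review, so the patient-reported side is largely protected. This stands. A reader might infer that recall is compromised because allocation follows consent ("Consented participants will be randomly allocated to one of the two study arms") and patients are asked to come only 15 minutes early. The document does not support that. Allocation is not itself treatment, the survey may be done by telephone or with a coordinator, and nothing says it must fit into those 15 minutes.

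Third, the direct t3 comparison is untouched by t0, and the sample size matches that comparison. This also stands and limits the damage. However, the article names no single main analysis, and it plans change and adjustment as well.

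Fourth, adjustment is conditional on clinically significant differences, so the adjusted figures apply only if it is triggered. This stands.

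**Conclusion.** The point holds in a limited form. As written, the t0 discrepancy count can differ between arms for reasons other than chance, and the plan then uses it as a clean baseline. Change and baseline-adjusted results for the primary endpoint can be biased, and the document does not settle the direction. The unadjusted t3 comparison does not share this weakness.

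The size depends on two assumed quantities, f and r. A change score loses (or, with the sign reversed, gains) the share f of the effect; an adjusted analysis loses or gains r·f.

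A reader might infer more: that the baseline is already treated, that the effect is therefore attenuated, and that power collapses. The documents do not support this. They do not show that the entry precedes the t0 review, and an inflated t0 count is as consistent with the text as a reduced one. Reaching a change estimate of zero would need the t0 count to fall by 1.56 of 3.12, which means one day's chart entry delivering the whole planned six-month effect.

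**What to change.** 1. In both arms, compute the t0 count only from the pre-review recall questionnaire and the last hepatology medication list dated before the allocation visit. Exclude the pharmacist's interview and entries.
2. At t3, use the same list-dating rule relative to the follow-up visit and the same sources in both arms, so that change compares like with like.
3. Use only these t0 values for baseline tables, change and covariate adjustment.
4. Name the between-group comparison at t3 as the main analysis.

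**Cost.** The Trial status section reports recruitment complete, so changing the order of survey and allocation is no longer open. The rule can still be applied by dated record extraction, provided the lists are dated, with no extra patients or procedures. The pre-visit list may be some months old, but equally so in both arms. Information from the reconciliation interview is lost to the primary count; it can still be reported descriptively for the intervention arm.
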